### Procedure

All study data will be collected remotely: online using Qualtrics, which is a well-established data collection platform, or on the phone by a trained researcher. For each participant, assessments will take place over the period of 4 weeks with measures taken shortly after consent (pre-baseline: sample characteristics measures and the feasibility question) and then at 1 week (baseline: questionnaires completed by parents, including economics measures), 2 weeks (adverse events collection) and 4 weeks (exit assessment) post-consent. Teachers will be contacted as soon as parents have provided their consent. Also, see Fig. 1.

**Fig. 1 Fig1:**
[figure not shown]
OPTIMA feasibility study flowchart. SDQ = Strengths and Difficulties Questionnaire; ADHD = attention-deficit/hyperactivity disorder; ODD = oppositional defiant disorder; LAC = looked after child; CAMHS = child and adolescent mental health services; OPTIMA = Online Parent Training for the Initial Management of ADHD referral

### Outcomes

The primary outcome for this study is the number of eligible feasibility study participants who *agree in principle* to take part in a full RCT of STEPS each month.

Agreement in principle to take part in the upcoming STEPS RCT: feasibility study participants will each be given a balanced explanation of what an RCT involves (see 2. Feasibility Question Script in Supplementary Documents) and asked. “*if there was an RCT of STEPS would they be willing to take part in it*?” After being asked the question parents will be given a choice of a YES/NO answer. Parents, who answer ‘NO’, will be asked to provide a brief explanation for their decision. The researcher will note a parent’s answer and any comments on the data form.

Secondary feasibility outcomes concerning the secondary study objectives are shown in Table 1.

**Table 1 Tab1:** Secondary feasibility outcomes

To pilot the remote consenting procedure, an online outcome and adverse events collection procedure.	To assess the feasibility of collecting teacher data remotely within the required timeframe.	To capture technical difficulties with completing online questionnaires.
*Remote consenting procedure:* • Mean time taken to complete remote consenting procedures. • Parents’ mean ratings of satisfaction with consenting procedures. • Content analysis of text box evaluations.	• Mean time to identify teachers. • The proportion of teachers’ questionnaires returned within 7 days of receiving a link to an online survey out of the number of teachers recruited	• Qualitative description of technical difficulties with accessing or completing online questionnaires.
*Online outcome collection:* • The proportion of participants completing outcome questionnaires within 7 days of receiving a link to an online survey out of the number of participants who are in the study. • Mean number of reminder emails about completing outcome questionnaires sent to parents by the research team. • Parents’ mean ratings of satisfaction with online data collection. • Content analysis of free text evaluations.		
*Online adverse events collection:* • The proportion of participants completing the adverse events questionnaire within 7 days of receiving a link to an online survey out of the number of participants who are in the study. • Mean number of reminder emails about completing adverse events questionnaire sent to parents by the research team.		

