## Methods

### Study objective

The primary objective of the study is to test whether we can use our remote recruitment, consenting and assessment strategy to recruit recent referrals to children’s services (CAMHS and early behavioural support services) at a sufficient monthly rate to provide statistical power for our planned STEPS RCT.

Secondary objectives include establishing the usability and acceptability of our remote recruitment, consenting and assessment strategy including the online outcome and adverse events collection procedure. We will also assess the feasibility of collecting teacher data remotely within the required timeframe and capture technical difficulties completing online questionnaires.

This study will not pilot or test the feasibility of the STEPS app as a form of a parent training intervention.

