### Consent

#### Parents

All participants will provide written informed consent to take part in the feasibility study. The informed consent form will be provided in electronic form using Qualtrics to be completed by the participant before they enter the study. The researcher will explain the details of the study, provide the Participant Information Sheet and will answer any questions that the participant has concerning the study. They will also inform parents that participation is completely voluntary, and they are under no obligation to take part and they can withdraw at any time without their care being affected. The researcher will also tactfully check whether it is a convenient time for a parent to commit to the study (i.e., if there is no expected imminent change to their existing care commitments, for example, late stage of pregnancy). On the consent form, there will be a separate statement requesting permission to contact the child’s teacher. If this box is not ticked, the teacher will not be contacted. If parents are unable to understand the consenting process it will be assumed that they do not meet the language requirement for the study.

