#### Teachers

Parents, who have given consent to contact their child’s teacher, will be asked to provide the name of their child’s school and the teacher’s name. The research team will then contact the teacher (by phoning or emailing a school) and invite them to take part in the study. An invitation will be followed up with an email containing a link to the teacher survey. This survey will include Teacher Information Sheet, a consent statement and a questionnaire. Teachers will also be invited to contact the research team with any questions that they might have about the study before they agree to take part.

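### Both teacher outcomes in Table 1 count only cases that have already succeeded, so neither shows how many families yield no identified or recruited teacher

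*Protocol article*

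**What the plan says.** The protocol article's Study objective section sets the aim: "We will also assess the feasibility of collecting teacher data remotely within the required timeframe". Table 1 (Outcomes) repeats it as a column heading and puts two outcomes under it.

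- The first is "Mean time to identify teachers". The table gives no population, start point, end point or rule for teachers who are not identified.
- The second is the proportion of teacher "questionnaires returned within 7 days of receiving a link to an online survey out of the number of teachers recruited".

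In the parents' column of the same table, the two completion proportions (outcome questionnaires and adverse events questionnaire) are taken "out of the number of participants who are in the study".

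The Consent section describes the route to a teacher. Permission is a separate item on the parent's consent form: "If this box is not ticked, the teacher will not be contacted". Parents who permit contact are asked to name the school and the teacher. Then: "The research team will then contact the teacher (by phoning or emailing a school) and invite them to take part in the study". An email follows with a link to one survey that holds the information sheet, the consent statement and the questionnaire.

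The Statistical analysis section plans descriptive and qualitative summaries for the secondary objectives and says that a quantitative analysis plan is being developed.

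**The concern.** Collecting teacher data takes a chain of steps: the parent permits contact, the teacher is identified, the teacher is recruited, and the questionnaire comes back in time. The objective asks about the whole chain. The first outcome describes the second link only where it succeeded. The second describes the last link only where all earlier ones succeeded. No listed outcome counts losses at permission, identification or recruitment.

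If the outcomes are reported as written, a short mean time and a high return rate could stand beside a low yield of teacher questionnaires per family. The planned RCT would then take from this study a favourable picture of teacher data that does not include the families for whom none was obtained.

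**Working it through.** The article states no expected time, identification rate or target for teachers, so there is no planned figure to reproduce. The check asks whether the two outcomes can tell a study that misses 10% of teachers from one that misses 40%.

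**Inputs.** From the article: 100 parents (Sample size) and a 4-week, or 28-day, parent assessment period (Procedure). Assumed: all 100 parents permit contact, 10% or 40% of teachers are missed, the identification times given below, and 28 days as the search limit where one is needed.

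**Case 1: misses unrelated to speed.** Take a mean of 7 days among those identified.
- Outcome as written: 7.0 days (n = 90) against 7.0 days (n = 60).
- Mean with missed teachers counted at 28 days: 0.9 × 7 + 0.1 × 28 = 9.1, against 0.6 × 7 + 0.4 × 28 = 15.4 days.

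**Case 2: slower identification, search ends at day 28.** Times are exponential with rate λ = −ln(m)/28, where m is the share missed. The mean among those identified is 1/λ − 28m/(1 − m).
- m = 0.1: 1/λ = 12.16, and 12.16 − 3.11 = 9.0 days.
- m = 0.4: 1/λ = 30.56, and 30.56 − 18.67 = 11.9 days.
- The underlying mean rises by 18.4 days and the reported one by 2.8 (9.05 to 11.89 before rounding).
- The median over all families, ln 2/λ, is 8.4 against 21.2 days.

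**Case 3: same speed, search given up sooner.** Times are exponential with mean 10 days, and the search stops at c = −10 ln(m). The mean among those identified is 10 − c·m/(1 − m).
- m = 0.1: c = 23.0, and 10 − 2.56 = 7.4 days.
- m = 0.4: c = 9.16, and 10 − 6.11 = 3.9 days.
- The outcome looks better although more teachers were missed.
- The censored median is 10 × ln 2 = 6.9 days in both, correctly showing unchanged speed. Only the proportion identified (90% against 60%) shows the loss.

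| | Mean as written, 10% missed | Mean as written, 40% missed | Direction |
|---|---|---|---|
| Case 1 | 7.0 days | 7.0 days | unchanged |
| Case 2 | 9.0 days | 11.9 days | rises |
| Case 3 | 7.4 days | 3.9 days | falls |

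**Second outcome.** Count every identified teacher as recruited and assume an 80% return within 7 days.
- As written: 72/90 = 80% against 48/60 = 80%.
- Out of all 100 parents: 72% against 48%.
- With a 60% return: 60% in both as written, against 54% and 36% per parent.

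So neither outcome, nor the two together, identifies the share missed. A proportion over all families does so in every case. A censored time summary adds the speed.

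**The case against.** The strongest reply is that this belongs to the analysis plan. Only a condensed article is at hand, that plan was still being written, and how to summarise a descriptive outcome or show counts is commonly left to it. Table 1 does not say that unidentified teachers are dropped or that no count will accompany the mean. This stands in part: the plan could add a censoring rule. But the article itself fixes the statistic (a mean) and the second denominator (teachers recruited), while using an all-participant denominator for parents. That is a choice already made, not a detail left open.

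A second reply is that the loss would not be wholly hidden. The number of teachers recruited must be known to compute the return rate, and a reader could set it against the number of parents. This is true but indirect. It does not separate refused permission, non-identification and non-recruitment. The article also does not say when a teacher counts as recruited. Because consent and questionnaire share one survey, a reading of recruited as consented would leave only teachers who had already opened the link.

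Four stronger readings are tempting and are not supported:

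- *The mean is the same whatever share is missed.* This holds only if misses are unrelated to speed (Case 1).
- *Non-identification is the main way teacher data fail.* Parents who permit contact are asked for the teacher's name and the school, and nothing suggests that 10% or 40% go unidentified. Refused permission or teachers not taking part may matter as much.
- *The mean is biased downward because the search stops at day 28.* The 4 weeks are the parents' assessment schedule, and Table 2 is labelled as covering parents only. No end of the teacher search is stated.
- *The decision to proceed to the RCT is at risk.* The Sample size section rests stop/go on 18 parents a month agreeing in principle, which does not use teacher data.

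**Conclusion.** The point holds in a limited form. Both teacher outcomes condition on earlier success, so as written they cannot show how many families yield no identified or recruited teacher, which is part of what the objective asks. That conclusion follows from the definitions and needs no assumed figures.

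Its size is unknown. The illustrations rest on assumed miss rates, identification times and, in Cases 1 and 2, a 28-day limit that the article does not set for teachers. They show that the mean can move in any direction, not how far it will move here. The outcome is secondary and descriptive, with no threshold attached. The change is worth making because it costs little and the result informs the RCT's teacher-data procedures.

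**What to change.** In Table 1, or in the analysis plan and report since the Study status section says recruitment is complete:

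1. Add the number and proportion of teachers identified, recruited, and returning the questionnaire within the required timeframe. Give each out of all participating parents, matching the parent outcomes, and out of parents permitting teacher contact. State when a teacher counts as identified and as recruited.
2. Report time to identification over all families permitting contact as a median, with unidentified teachers censored at a stated cut-off. If fewer than half are identified by then, report the median as not reached.
3. If a mean or the 7-day return among recruited teachers is kept, show the number identified or recruited beside it.

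The cost is a few lines of text and a short table. The planned mean already needs start and identification dates, and permission is recorded on the consent form, so no new participant data should be needed. The only downside is that the reported figures may look less favourable.

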### Measures and procedure

Figure 1 shows the study flowchart.

#### Pre-baseline measures

These will be collected directly online using Qualtrics or on the phone and entered by the researcher into Qualtrics to characterise the sample and will consist of the following questionnaires (for participant timeline see Table 2):

**Table 2 Tab2:**
[figure not shown]
Feasibility study timeline (parents only)

Eyberg Child Behavior Inventory [21] is a 36-item measure of conduct problem behaviour for children aged 2–17 years. Parents rate behaviour occurrence on a 7-point scale ranging from never to always and the item ratings are summed to yield the Intensity score. Parents also indicate whether the behaviour is a problem at present by answering “yes”/“no”. The yes responses are summed to produce a Problem score.

Social Communication Questionnaire [22] is a 40-item screening measure for autism spectrum disorder (ASD). It is based on the Autism Diagnostic Interview-Revised [23] and validated to use for ages 4 years and above. Questions focus on behaviours that are likely to be observed by the primary caregiver and concern the following domains: reciprocal social interactions, language and communication and repetitive and stereotyped patterns of behaviours. The presence of autism-positive behaviour is coded as 1 and its absence as 0. Because the first question concerns the level of current language and as is not included in the total score, for children with language, the maximum score is 39; for children without language, the maximum score is 33 (language items are inapplicable). The recommended cut-off score for cases requiring further investigation is 15. Due to the high levels of clinical co-existence of ASD and ADHD [24], this questionnaire is used to describe how much ASD there is in this population.

ADHD subscale of the Swanson, Nolan and Pelham Rating Scale-the MTA version (SNAP-IV) [25]. The SNAP-IV is a behavioural rating scale that captures the core symptoms of ADHD and ODD. The ADHD subscale of SNAP-IV consists of 18 items that are rated on a 4-point scale (not at all, just a little, quite a bit, very much). The subscale scores are obtained by averaging responses regarding inattentive and hyperactive/impulsive symptoms. Scores above the 95th percentile are considered clinically significant. The questionnaire has established validity and reliability [26].

We will also obtain information about the child’s general practitioner’s name and address and a teacher’s name and the name of the school (if a parent consented to teacher contact).

#### Baseline measures—parents

At baseline, parents will answer demographic questions and complete clinical outcome and health economics measures online using Qualtrics (also see Table 2).

##### Demographics questionnaire

Information about the child’s age, gender, ethnicity, parental education, socio-economic status and family structure (specifically, about marital status).

##### Clinical outcome measures

The ODD subscale of the SNAP IV [25]. This subscale consists of eight items that are rated on a 4-point scale (not at all, just a little, quite a bit, very much). The subscale score is obtained by averaging responses. Scores above the 95th percentile are considered clinically significant. The questionnaire has established validity and reliability [26].

The O’Leary Parenting Scale [27] will be used to examine changes in parenting style. Parents will rate their probabilities of using specific discipline strategies in response to child misbehaviours. Responses are made on a 7-point scale. Only items that map onto the three factors: laxness (lack of consistent responding; 5 items), over-reactivity (overly emotional or harsh responding; 5 items), hostility (hostile verbal and physical behaviour towards the child; 3 items) will be included.

The Parental Sense of Competence scale [28] will be used to measure parenting satisfaction. The scale has 16 items and parents make responses on a 6-point scale, with options ranging from strongly disagree to strongly agree. Two indices are calculated for each participant: efficacy, which reflects domain-general parenting self-efficacy and satisfaction, which reflects the degree of anxiety, frustration and motivation associated with the parental role.

Caregiver Strain Questionnaire (CGSQ) [29]. CGSQ is a 21-item measure of self-reported strain experienced by caregivers and families of children with emotional and behavioural problems, with responses made on a 5-point Likert scale. It consists of three subscales: Objective Strain, Subjective Internalised Strain and Subjective Externalised Strain. Global Caregiver Strain Score is determined by calculating the mean of all items on the CGSQ.

##### Economic measures

Child and Adolescent Service Use Schedule (CA-SUS) [30], a measure of service use applied in a range of populations of young people with mental health problems. The CA-SUS will be completed by the primary carer at baseline (covering the previous three months). The CA-SUS collects information on the use of all hospital and community-based health services, social care and education services, service-provided accommodation (for example, Local Authority foster or residential care) and all prescribed medications.

Child Health Utility Index (CHU-9D) [31]. The CHU-9D is a paediatric preference-based quality of life measure for use in healthcare resource allocation decision-making. The CHU-9D has been designed for self-report by children aged 7 to 17, but with an interviewer’s help, can also be used in children as young as 6 years old [32] and guidance is available from the developers for proxy completion by parents for children aged 5 and under. The questionnaire includes 9 items, each with a 5-level response category. Each item taps into a different domain of children’s present functioning: worry, sadness, pain, tiredness, annoyance, school, sleep, daily routine and activities. The present study does not involve collecting data from children; therefore, a proxy version will be used for all.

#### Baseline measures—teachers

Teacher data will be collected online using Qualtrics and will consist of the ODD subscale of the SNAP-IV [25].

#### Adverse events

Parents will be asked to report any physical and mental health difficulties or events for themselves and their child that have occurred since the start of the study. This information will be collected online during week 2 to pilot the adverse event collection procedure (see Table 2). A more detailed description of adverse events recording and reporting is provided in ‘Adverse events management’.

#### Exit interview: evaluation of acceptability

At the end of week 4, parents will be emailed a link to a brief evaluation questionnaire (see Table 2). The questionnaire will aim to collect information about parents’ satisfaction with remote data collection and their feedback about study procedures. Responses will be provided using structured Likert-type scales and free text boxes.

### Participant timeline

Table 2 shows a detailed schedule concerning the study timeline for parents participating in the study.

### Sample size

The primary aim of the feasibility study is to establish that we can recruit enough parents of new referrals for the STEPS RCT using our remote strategy incorporating existing routine CAMHS triage and clinical screening elements using MHE, ICAN or telephone-based methods across the five recruitment sites (Fig. 2). Based on the power calculations for the larger planned RCT of STEPS, we need to recruit 13 participants a month (352 families over 27 months). We will base our assessment of whether this is possible on the primary feasibility outcome described above, the rate per month of participants who answer the STEPS RCT feasibility question in the affirmative. Because we assume it is more likely that people would agree in principle to take part in STEPS RCT during the feasibility study than would actually consent to the real trial, we have adopted a conservative requirement in this feasibility of 18 (rather than 13) parents a month as our aim in this feasibility study and our stop/go criterion for the larger trial.

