**Fig. 2 Fig2:**
[figure not shown]
Estimated monthly referral flow

The numbers of potential participants at each stage of the selection process during each month of the feasibility study is shown in Fig. 2. Based on audit and best information across our trial sites, we estimate that each month, parents of 200 newly referred children (of roughly 750 referrals across the 5 sites) will be eligible to take part in the feasibility study. We estimate that 50 parents would consent to the feasibility study and of these roughly 25 will give a positive response to the feasibility question, which is above the number required.

We will test this by recruiting 25 study eligible parents (half of the number available) each month (100 over 4 months). Our projections will be supported if 12 or so of these parents answer the feasibility question positively. This number will also give us a good sample in which to assess our other feasibility measures.

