### Statistical analysis

This feasibility study will not use inferential statistics to assess the primary objective but will estimate the rate per month of eligible participants who agree in principle to take part in the upcoming STEPS RCT (with the aim of getting 18 per month to give sufficient statistical power to evaluate STEPS in the larger trial planned for later in the programme). Other objectives will be met by using descriptive statistics and qualitative assessments in combination to study the efficiency and acceptability of aspects of the proposed methods. Neither subgroup nor interim analyses are planned in this study. A quantitative statistical analysis plan is being developed.

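### The stop/go criterion of 18 'yes' answers a month belongs to the full projected flow, but the outcome it is applied to is counted in a sample of 25 parents a month, and no conversion is stated

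*Protocol article*

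**What the plan says.** The Outcomes section defines what is counted: "The primary outcome for this study is the number of eligible feasibility study participants who" say they would join a full trial of STEPS, taken month by month. It is a count of people enrolled in the feasibility study.

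The Sample size section begins with the need of the later trial: "we need to recruit 13 participants a month (352 families over 27 months"). It bases the judgement on "the rate per month of participants who answer the STEPS RCT feasibility question in the affirmative". Because saying 'yes' in principle is easier than consenting to a real trial, it raises the bar to "18 (rather than 13) parents a month as our aim in this feasibility study and our stop/go criterion for the larger trial".

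The Statistical analysis section says the monthly rate will be estimated "with the aim of getting 18 per month to give sufficient statistical power to evaluate STEPS in the larger trial". It gives 18 as an aim and does not use stop/go wording.

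The text after Fig. 2, still under Sample size, gives the projection: "We estimate that 50 parents would consent to the feasibility study and of these roughly 25 will give a positive response to the feasibility question". It notes that this exceeds the requirement. It then describes what will be done: "We will test this by recruiting 25 study eligible parents (half of the number available) each month (100 over 4 months"). The expected result follows: "Our projections will be supported if 12 or so of these parents answer the feasibility question positively".

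Under Data monitoring, the Programme Steering Committee meets at the end of the study to decide whether to go on to the trial.

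**The concern.** The threshold and the count are on different scales. Eighteen a month is a modest requirement when 50 parents consent and about 25 say 'yes'. It is a severe one when at most about 25 parents are asked each month. The Outcomes, Sample size and Statistical analysis sections all speak of a monthly number or rate of participants, and none gives a factor for moving from the 25 recruited to the 50 assumed available.

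Whether to proceed to the trial is the main decision this study serves. If the projection proves exactly right, the text after Fig. 2 calls it supported, while the stop/go sentence, read as written, says the criterion was missed. The Steering Committee would have to choose a reading after seeing the data, which a criterion fixed in advance is meant to prevent.

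**Working it through.** **Inputs, all from the Sample size section and the text after Fig. 2.** Trial need: 352 families in 27 months. Criterion: 18 'yes' a month. Projected full flow: 50 consenting and about 25 'yes' a month. Planned recruitment: 25 a month for 4 months. Expected result: 12 or so 'yes' a month.

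**Step 1. The plan's own figures reproduce.**
- 352 / 27 = 13.04 a month, and 13 × 27 = 351.
- 25 × 4 = 100 parents.
- Projected 'yes' proportion: 25 / 50 = 50%.
- Expected 'yes' among those recruited: 25 × 0.50 = 12.5 a month.

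There is no arithmetic slip in the stated numbers. The problem is which count the 18 is compared with.

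**Step 2. Literal reading: 18 observed 'yes' answers among 25 recruited.**
- Required proportion: 18 / 25 = 72%. Over four months: 18 × 4 = 72 of 100.
- With X ~ Binomial(25, 0.50), P(X ≥ 18) = 0.022.
- With Y ~ Binomial(100, 0.50), P(Y ≥ 72) = 6.3 × 10⁻⁶.
- If the true proportion were 60%, above projection, the same probabilities are 0.154 and 0.008.

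**Step 3. Scaled reading: the 25 recruited stand for 50 available.**
- Scaling factor: 50 / 25 = 2. A month with 12 of 25 becomes 12 / 25 × 50 = 24, above 18.
- Equivalent mark on the observed scale: 18 / 50 = 36%, which is 0.36 × 25 = 9 of 25, or 36 of 100.
- At a true 50%, P(at least 9 of 25) = 0.946 and P(at least 36 of 100) = 0.998.

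**Step 4. What the scaling rests on.** If F parents a month would consent and a proportion p say 'yes', the full-flow rate is F × p, and reaching 18 needs p ≥ 18 / F. Recruiting 25 a month does not by itself show how many more would have consented, so F is an assumption. The range is:

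| Assumed consenting flow F per month | 'Yes' proportion needed |
|---|---|
| 50 (the plan's projection) | 18 / 50 = 36% |
| 36 | 18 / 36 = 50% |
| 25 (only those recruited) | 18 / 25 = 72% |

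At the projected 50% 'yes', the criterion is met only if at least 36 parents a month would consent.

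**Step 5. Where the two written statements part company.** A monthly mean from about 12 to 17 supports the projection and falls short of 18. The expected value of 12.5 lies inside that range.

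**The case against.** The strongest reply is that the text contains its own reconciliation. The 25 recruited are described as half of those available, and recruiting them is presented as a test of the full-flow projection. On that reading 12 of 25 stands for about 24 a month, which clears 18. This is probably what was meant, and a reader who infers that the target is unreachable goes too far. The probabilities in Step 2 belong to the literal reading and to a 50% 'yes' proportion. What remains is that the conversion is written nowhere, that the stop/go sentence sets 18 as the aim within this feasibility study, and that doubling relies on a flow of 50.

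A second reply is that 12 is not a go mark. That is correct. The protocol says only that such a result would support its projections, and the single number it labels stop/go is 18. The link to the decision is indirect: the projection being checked is the one described as exceeding the requirement. A reader might also see three competing thresholds (18, 12 and 9) and a zone of conflict from 9 to 17. The documents do not support that. Nine appears nowhere in them and is only 18 rescaled. Below about 12, both written figures are unfavourable, allowing for the looseness of '12 or so'.

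A third reply is that the analysis plan, still in development when the article was written, may define the estimator. It may, and its absence here is no fault. But the mismatch lies between statements already made in the protocol, so an analysis plan would need to correct the stop/go sentence as well as add to it.

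**Conclusion.** The point holds as a mismatch of scale with an unstated conversion. At the plan's own 50% 'yes' proportion, the chance of meeting the criterion over 100 parents is about 6 in a million on the literal reading and 0.998 on the scaled reading, so the reading settles the decision. These figures assume independent answers with a constant 'yes' probability and full recruitment of 25 a month. They are used only to show size, since the study plans no inferential test of its primary objective. The scaled figure also assumes that 50 parents a month would consent. The conclusion does not depend on Fig. 2, which is not shown, because the text gives the numbers used here.

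**What to change.** State one decision quantity and one threshold, and use them in the Outcomes, Sample size (including the text after Fig. 2) and Statistical analysis sections. Either of two forms would do:

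1. **Observed scale.** The criterion is met if at least 36% answer 'yes' (9 of 25 a month on average, 36 of 100 overall), conditional on evidence that about 50 consenting parents a month are available.
2. **Scaled rate.** State the rule that turns the observed count into a full-flow monthly rate, including where the flow figure comes from, and compare that rate with 18.

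In both forms, label '12 or so' as the expected value and not a decision mark, and report the raw and the scaled counts side by side.

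The cost is mainly wording, plus counts from screening and consent logs to confirm the flow. The article does not list eligible flow or consent proportion among its outcomes, so the team should check that these counts were kept. The Study status section reports that recruitment has finished, so the change can no longer act as a prospective rule. The conversion should therefore be declared openly in the analysis plan and the report, with a statement of when it was fixed relative to sight of the data.
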